### Cost utility analysis

A CUA will be conducted similarly to that described above, whereby the EQ5D will be completed at baseline, and at 6 months and 12 months. The UK tariff [48] will be used to value the health states and QALYs will be estimated using the area under the curve method [49]. An ICER using the cost per QALY gained will be estimated, and in this instance can be more informative than cost per improvement in JAFI, as should the intervention prove to be more effective but also more costly, then it is possible to compare the cost per QALY gained with the National Institute for Health and Clinical Excellence (NICE) threshold.

Notably the EQ5D has only been validated for use in adults, and while there is a child version available, it has not yet been validated. In order to explore the issue of child responses versus parent proxies, given that the target population includes children as well as adults who developed JIA as a child, it is proposed that the children in the study will complete the child version of the EQ5D, while their parents will complete the adult version on behalf of their children. The resulting scores will be compared, and will be used to inform a sensitivity analysis of the CUA to determine whether they influence any decision on value-for-money.

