### Randomisation

Treatment allocation will be conducted by means of minimisation, a highly effective method of allocation which has been recommended for use in randomised controlled trials [33]. Using this method, treatment allocated to the next trial participant depends on the characteristics of those participants already enrolled, with the ultimate aim of 'minimising' the imbalance between groups [34]. Minimisation in this case will be adopted to achieve balance between groups using the following characteristics:

(i) Age

(ii) Gender

(iii) JAFI-IMP score

This method will be conducted by the same researcher (GH) using the minimisation software package Minim [35].

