Power Doppler	Display of signal flow in the synovium	0- No flow
		
		1- Single vessel signals
		
		2- Confluent vessel signals in less that half of the synovium
		
		3- Vessel signals in more than half of the area

To objectively measure lower limb and foot function, spatiotemporal gait parameters (walking speed, double-support time and symmetry index) will be assessed using an instrumented walkway (GaitRITE, CIR systems, Clifton, NJ, USA). Plantar pressure and force distribution will be measured using a pressure platform (Emed NT, Novel GmbH, Munich, Germany) using standardised protocols as previously developed in adult rheumatoid arthritis and JIA research [27,39,40]. From the gait analysis, six key variables will be selected: peak pressure in the forefoot; contact area in the toes; contact area in the midfoot; transfer of centre of pressure through the foot, and the peak ground reaction force during the loading response and terminal stance phases. Walking speed (m/s), stride length (m), cadences (steps/min), cycle time (% gait cycle), and double support time will be selected as a core set of spatiotemporal gait parameters and compared against age/gender normative values [27,39].

Arthritis activity measures will be assessed using the Core Outcome Variables for JIA, a validated clinical assessment for disease activity which correlates with adult measures. JIA patients under 16 years will have the Core Outcome Variables recorded (consisting of the CHAQ questionnaire completed by the patient or parent, active and limited joints, and physician global assessment completed by the doctor in clinic). For adults with JIA these will be the physician global assessment, pain assessment, number of tender, swollen and deformed joints and duration of early morning stiffness and HAQ. These adult and paediatric measures are comparable. The Glasgow Enthesitis Score, a non-validated measure of enthesitis severity, will be recorded by the examining doctor in all patients.

A variety of secondary outcomes will be recorded at baseline and at the final study visit (12 months from baseline). The Childhood Health Assessment Questionnaire (CHAQ) and the Health Assessment Questionnaire (HAQ) will be used as measures of overall function/disability in children/adolescents and adults respectively [41,42], while the EQ5D will be employed to measure general HRQoL, and will be used specifically within the economic evaluation [43].

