#### Patient follow up procedures

All participants regardless of allocation will undergo another full assessment once they have proceeded to the end of the trial (12 months from baseline). In the interim period, the primary outcome questionnaire (JAFI) will be posted at 6 months from baseline with a stamped-addressed envelope in order to complete and return to the study personnel. Non-responders will be sent a second questionnaire within 2 weeks, followed by a third a further two weeks later, and then contacted by written letter/telephone. Participants in the intervention arm will receive return appointments every 3 months. Any additional appointments within the intervention arm will be made within the scope of normal clinical practice.

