### Cost effectiveness analysis

As described above, at baseline JAFI will be recorded. Health care resource use will be collected from patient notes and parents/adult suffers will also provide details of other health care use (primary care use), out-of-pocket expenses and productivity loss using a self-completing questionnaire. Health care resource use will be valued using national published costs [45-47] while lost productivity will be valued using the human capital approach.

At 6 and 12 months from baseline outcomes will be reassessed. The difference in outcome between baseline and 6 and 12 months will provide a measure of effectiveness. Costs incurred during the trial will be aggregated to represent an annual cost, and both direct health care costs and indirect/societal costs of the intervention and standard care will be calculated. The economic analysis will compare the costs and outcomes in each arm, and it will estimate the (additional) cost per (additional) unit of improvement of the JAFI, which will be presented in the form of an incremental cost effectiveness ratio (ICER). Confidence limits for the ICER will be estimated using bootstrapping, and the analysis will also produce cost effectiveness acceptability curves (CEACs), which provide a presentation of uncertainty in terms of the threshold of acceptability.

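### The QALY comparison names no adjustment for baseline EQ5D, so chance baseline imbalance partly enters the incremental QALY and precision is lost; the EQ5D schedule behind it also conflicts between sections

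*Protocol article*

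**What the plan says.** All references are to the protocol article.

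- **Cost utility analysis.** On timing: "whereby the EQ5D will be completed at baseline, and at 6 months and 12 months". On construction: "QALYs will be estimated using the area under the curve method", using the UK tariff. The result is a cost per QALY that may be set against the NICE threshold. The section opens: "A CUA will be conducted similarly to that described above".
- **Cost effectiveness analysis**, the section this refers back to. "The economic analysis will compare the costs and outcomes in each arm". Effectiveness there is measured as the difference from baseline at 6 and 12 months. Uncertainty is handled by bootstrapping the ICER and by acceptability curves (CEACs). No covariate is named.
- **Randomisation.** "Minimisation in this case will be adopted to achieve balance between groups using the following characteristics": age, gender and JAFI-IMP. EQ5D is not among them.
- **Initial assessments and outcome measures.** "A variety of secondary outcomes will be recorded at baseline and at the final study visit (12 months from baseline". The EQ5D is listed in that paragraph.
- **Patient follow up procedures.** At the interim contact, "the primary outcome questionnaire (JAFI) will be posted at 6 months from baseline". No EQ5D is mentioned there.

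**The concern.** Area under the curve defines each patient's QALY. It does not define how the arms are compared. The only comparison described sets outcomes in one arm against the other, with nothing said about baseline utility.

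Baseline EQ5D enters the result twice. It is part of the area itself, and it correlates with the later scores. It is measured before treatment, so any difference between arms at that point is chance. Minimising on JAFI-IMP protects only as far as JAFI-IMP and EQ5D are related. Bootstrapping and acceptability curves display the resulting spread but do not remove the imbalance from the point estimate.

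Cost effectiveness is part of the stated primary aim, and the incremental QALY is the denominator of the ICER. A small denominator can be shifted, or change sign, through a pre-treatment difference. The interval around it is also wider than the planned data require.

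**Working it through.** **Plan's own figure.** None exists for EQ5D or QALYs. The Sample size section concerns JAFI-IMP only and supplies just the numbers of patients: 30 per arm, with 8 per arm allowed for drop-out by six months (leaving 22).

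**Assumptions, not in the document.** Equal EQ5D SD at each visit of 0.25 (range 0.20-0.30), and a common between-visit correlation rho of 0.5 (range 0.3-0.7).

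**1. Weights.** With EQ5D at 0, 6 and 12 months, the trapezoid rule gives QALY = 0.25·U0 + 0.50·U6 + 0.25·U12.

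**2. Likely chance imbalance.** SE of the baseline difference = 0.25 × √(2/30) = 0.0645.

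**3. Share passed on.** The slope of the QALY difference on the baseline difference is 0.25 + 0.75·rho: 0.475, 0.625 and 0.775 at rho 0.3, 0.5 and 0.7. A one-SE imbalance therefore moves the incremental QALY by 0.031, 0.040 or 0.050.

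**4. Precision.** In units of SD²:

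- Raw variance = 0.375 + 0.625·rho. At rho 0.5 this is 0.6875.
- Adjusted variance = raw variance − slope². At rho 0.5 this is 0.6875 − 0.625² = 0.2969.
- Change-from-baseline variance (weights −0.75, 0.50, 0.25) = 0.875·(1 − rho). At rho 0.5 this is 0.4375.

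The SE is 0.0645 times the square root of each:

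| rho | SE raw | SE change from baseline | SE adjusted | Variance saved vs raw | Variance saved vs change |
|---|---|---|---|---|---|
| 0.3 | 0.0484 | 0.0505 | 0.0375 | 40% | 45% |
| 0.5 | 0.0535 | 0.0427 | 0.0352 | 57% | 32% |
| 0.7 | 0.0582 | 0.0331 | 0.0297 | 74% | 19% |

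The percentages do not depend on the SD. With 22 per arm at rho 0.5, the SEs are 0.0625 raw and 0.0411 adjusted.

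**5. Simulation check** (10,000 trials, rho 0.5, 30 per arm). SE was 0.0534 raw and 0.0353 adjusted. Correlation of the estimate with baseline imbalance was 0.75 raw and 0.00 adjusted.

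**6. Allowing for minimisation on JAFI-IMP.** Suppose JAFI-IMP is fully balanced, correlates r with baseline EQ5D, and relates to later EQ5D only through it. The baseline part of the variance then shrinks by the factor 1 − r². At rho 0.5:

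- r = 0.5: 0.3906 × 0.75 = 0.2930; saving = 0.2930 / (0.2930 + 0.2969) = 50%.
- r = 0.7: 0.3906 × 0.51 = 0.1992; saving = 0.1992 / (0.1992 + 0.2969) = 40%.

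**7. If change from baseline is meant.** The slope becomes −0.525, −0.375 and −0.225. The arm that starts higher is now penalised.

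**8. If EQ5D is taken only at 0 and 12 months.** The weights become 0.50 and 0.50, and the slope 0.50 + 0.50·rho (0.65-0.85). At rho 0.5 the SE is 0.056 raw and 0.028 adjusted.

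**The case against.** The strongest reply is that the text is silent. A reader might infer that the plan excludes adjustment and uses baseline EQ5D only to build the area. The article does not say that: regression on baseline is fully compatible with area-under-the-curve QALYs, and a condensed article may leave covariates to a fuller plan. This stands against calling it a declared choice. It does not remove the case for naming the estimator, because the section already fixes the tariff, the QALY construction and, by reference back, the interval method.

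Second, the cross-reference to the cost effectiveness section can be read as importing change from baseline, which is itself a crude correction. That is a fair reading, and it alters the sign and size of the problem. It does not alter the remedy, since regression has the smaller SE at every rho considered. Two readings with opposite dependence on baseline are a further reason to settle the wording.

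Third, a reader might infer that the raw contrast is biased, or that a baseline difference is credited in full as QALYs gained. Neither holds. Randomisation keeps the raw estimate unbiased on average, and only part of an imbalance carries over.

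Fourth, the trial is exploratory and plans no QALY test or QALY power, so the gain should be stated as precision of the incremental QALY, not as power. This stands.

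**Conclusion.** The point holds as one of conditional imbalance and lost precision, in an analysis whose between-arm estimator is left open. Under the raw reading, roughly half to three quarters of a chance baseline difference would enter the incremental QALY. Adjustment would save about 57% of the variance at rho 0.5 (40-74% over rho 0.3-0.7), or about 40-50% at rho 0.5 once partial balance through JAFI-IMP is credited. Under the change-from-baseline reading the saving is about 19-45%.

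All of these sizes rest on the assumed correlations, equal variances and a common rho; the absolute SEs also rest on the assumed SD. That adjustment is the most precise of the three estimators holds throughout the range examined.

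The schedule conflict rests on no assumption. One section has EQ5D at three time points, another lists it among outcomes taken at baseline and 12 months, and the 6-month mailing names only the JAFI. The weights cannot be settled until these agree.

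**What to change.** In the Cost utility analysis section:

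1. Keep the area-under-the-curve QALYs. Estimate the between-arm QALY difference by regressing QALYs on arm, baseline EQ5D (the same version and respondent as used for that patient's QALYs), age, gender and baseline JAFI-IMP.
2. Refit this regression within each bootstrap replicate, so that the ICER, its confidence limits and the acceptability curve all use the adjusted difference.
3. Say whether the reference back to the cost effectiveness section covers costs and uncertainty only, or also the change-from-baseline effect measure.
4. Reconcile the EQ5D time points across the Cost utility analysis, Initial assessments and outcome measures, and Patient follow up procedures sections, and state the resulting area-under-the-curve weights.

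Items 1 to 3 cost a few sentences and a few degrees of freedom in about 60 patients. They need no new data, because baseline EQ5D is already planned for collection. Item 4 is a wording change if the 6-month EQ5D is already intended; otherwise it means either adding the EQ5D to the existing 6-month mailing or moving to a two-point QALY.

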#### Economic evaluation

An economic evaluation aims to assess whether an intervention provides value-for-money relative to its comparator. There are three approaches which can be employed to assess this: cost-effectiveness analysis (CEA), cost utility analysis (CUA) and cost benefit analysis (CBA). This trial provides a unique opportunity to not only assess value-for-money but also consider the issue of outcome measurement in children and adults where parents are used as a proxy respondent, and to further explore the aspects surrounding parental and patient preferences for health care. Therefore, a relatively exhaustive evaluation is proposed which will utilise all three of the economic evaluation approaches.

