### Sample size

The sample size for the study has been pre-determined by power analysis of the primary outcome measure; the impairment domain of the JAFI questionnaire (JAFI-IMP. Sixty patients (30 in each trial arm) will allow detection of a 1 point reduction in the JAFI-IMP score (a conservative assumption determined by the trial steering committee) at six months from baseline at a significance level of p < 0.05 and power of 90%. These figures take into account the estimated potential participant drop out rate over the first six months of the trial (8 patients in each trial arm). The exploratory nature of the trial will permit in-depth examination of the suitability of the JAFI as a primary outcome measure for use in definitive multi-centre trials.

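### In child participants EQ5D version goes with respondent, so a child–parent difference in scores, or its absence, cannot be attributed to who answered

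*Protocol article*

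**What the plan says.** The Economic evaluation section presents the trial as a chance to "consider the issue of outcome measurement in children and adults where parents are used as a proxy respondent". The Cost utility analysis section makes this specific to the EQ5D. It gives the purpose ("In order to explore the issue of child responses versus parent proxies") and the allocation of forms: "the children in the study will complete the child version of the EQ5D, while their parents will complete the adult version", the parents answering for their children.

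Three further statements in that section matter here:

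- On validation: "the EQ5D has only been validated for use in adults, and while there is a child version available, it has not yet been validated".
- On valuation, one tariff is named: "The UK tariff [48] will be used to value the health states". Nothing separate is given for the child version.
- On use: "The resulting scores will be compared, and will be used to inform a sensitivity analysis of the CUA", the question being whether the choice affects the value-for-money decision.

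The section on initial assessments and outcome measures mentions the EQ5D only as a general quality-of-life measure for the economic evaluation. No section has a parent complete the child version, or a child complete the adult version.

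**The concern.** A comparison of child self-report with parent proxy needs the two respondents to answer the same instrument. Here each respondent has a different one, so who answered and which form was used change together. If the scores differ, the reason could be the respondent, the form, or both. If they agree, there may be no effect of either, or two effects that offset each other.

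The protocol itself closes the easy way out, which would be to treat the versions as interchangeable: it says that one is validated only in adults and the other not at all. Because the problem lies in what is collected, no later analysis plan can repair it. At stake is what this exploratory trial can say about choosing a respondent, or a form, in a later definitive trial.

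**Working it through.** The protocol states no figure for this comparison, so there is none to reproduce. The check is whether the respondent effect can be estimated from the data to be collected.

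**Inputs** (Cost utility analysis section). Two of the four possible respondent-by-version combinations are collected for each child: child on child version, and parent on adult version.

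**Model.** Expected score = m + r × (parent answers) + v × (adult version), where r is the respondent effect and v the version effect. Anything that arises from applying the single named tariff to the child form is part of v.

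| Combination | Intercept | Parent | Adult version | Expected score |
|---|---|---|---|---|
| Child, child version | 1 | 0 | 0 | m |
| Parent, adult version | 1 | 1 | 1 | m + r + v |

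The last two indicator columns are identical. The design matrix has rank 2 for 3 parameters, and the only estimable contrast is parent minus child = r + v.

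**Illustration** (assumed effects, to show the algebra only):

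| r | v | Observed r + v |
|---|---|---|
| -0.10 | 0 | -0.10 |
| 0 | -0.10 | -0.10 |
| -0.05 | -0.05 | -0.10 |
| +0.10 | -0.20 | -0.10 |
| -0.10 | +0.10 | 0 |

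The first four rows give the same data. The last gives perfect average agreement despite a respondent effect of -0.10. More patients narrow the interval around r + v but do not split it.

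**Can the adult patients supply the missing link?** They add the combination self-report on adult version, but in different people, so an age-group term is needed. That makes 4 parameters with rank 3, and r remains non-estimable.

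**With one more combination.** If parents also complete the child version, the row (1, 1, 0) is added and the rank becomes 3 of 3:

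- Parent minus child, both on the child version: (m + r) - m = r. This is a paired contrast on one form and needs no further assumption.
- Parent's adult version minus parent's child version: (m + r + v + i) - (m + r) = v + i, where i is any respondent-by-version interaction. It equals the version effect for children's own reports only if i = 0.

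**Does the aliasing bias the cost per QALY?** With EQ5D at 0, 6 and 12 months and the area-under-the-curve method, QALYs = 0.25 × u0 + 0.50 × u6 + 0.25 × u12. A constant shift c in every child's utility adds c × (0.25 + 0.50 + 0.25) = c to each child's QALYs. If the arms hold the same share of children, which minimisation on age works towards, the shift cancels in the between-arm difference. Only a shift that varies by arm, over time or with health state would alter that difference, and the documents give no figure for one.

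**The case against.** The strongest defence is that the comparison has a practical end use that survives. The section wants to know whether the choice of scores influences the value-for-money decision. That is a scenario analysis: calculate the result with the children's scores, then with the parents' scores, and see whether the decision changes. It needs only the combined difference. Whether the two approaches give different scores in the same children can also be answered. All of this stands.

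A reader might go further and infer any of three things, none of which the documents support:

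- **That the sensitivity analysis is invalid, or will move the cost per QALY for a spurious reason.** The scenario analysis is feasible, and a constant shift cancels between balanced arms. Patients know their allocation (Blinding section), so an arm-dependent parental effect is conceivable, but nothing in the documents shows or quantifies one.
- **That the sponsor will read a difference as proxy bias and agreement as proof that proxies are acceptable.** The protocol says only that the scores will be compared and will inform a sensitivity analysis.
- **That nothing about child and proxy scores can be learned.** The two packages can be compared; the reason for a difference cannot be found.

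It is also fair to say that the aim is worded as exploration, and that the Economic evaluation section's remark on proxies is general and not tied to the EQ5D. Even so, the Cost utility analysis section names child responses against parent proxies as the reason for this data collection, and the forms chosen cannot isolate that contrast.

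**Conclusion.** The point holds as a limited one. In child participants respondent and EQ5D version are completely aliased, so neither a difference nor agreement can be attributed to who answered. This follows from the stated allocation of forms and rests on no assumed effect size. It assumes only that a version effect cannot be ruled out, which the protocol's own remarks on validation support.

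Its reach is one exploratory question within one of three economic analyses, in the children and adolescents of a 60-patient trial. The JAFI-IMP comparison, between-arm comparisons within either EQ5D source, and the check of whether the decision changes with the score set are all unaffected. It merits action because the remedy is cheap and lets the trial answer a question that it poses itself.

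**What to change.** **Preferred.** Have the parents of participating children also complete the child version as proxy, at each EQ5D time point and alongside the adult version. Name child versus parent on the child version as the paired respondent contrast. Report the parent's child version against the parent's adult version as the version contrast, and state that it carries over to children's self-reports only if there is no respondent-by-version interaction.

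**Cost.** One extra short form per parent per time point, so three in all under the schedule in the Cost utility analysis section, with no extra visit. Two similar forms completed together may carry over into each other. The documents do not say whether the child version suits proxy completion, so the sponsor should confirm this first.

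**If declined.** Restate the aim as a comparison of two combined measurement approaches: child self-report on the child version, and parent proxy on the adult version. Keep the scenario analysis, and state that the difference will not be interpreted as a proxy effect. This costs only a change of wording.
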